**Fig. 3 Fig3:**
[figure not shown]
Conceptual framework

#### Providers

Through departmental staff meetings and direct invitations, the study team will contact eligible providers. Those who consent (via information sheet) will be randomized. Intervention arm providers will be invited to a 1-h training on the study, use of individualized preventive care recommendations and shared decision-making [36–39]. Those who complete the training will receive access to individualized preventive care recommendations in the EHR.

#### Patients

Through automated data feeds from the EHR linked with upcoming appointment schedules, and manual chart review as needed, the study team will identify specific patients. We will ask if the patient’s provider is willing to discuss individualized recommendations with this patient. The team will seek to enroll the patient and remind providers shortly before the scheduled encounter.

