**Methods:**

The Personalized Disease Prevention (PDP) cluster-randomized clinical trial will evaluate whether patients and their providers benefit from an evidence-based decision tool to prioritize preventive services based on their potential to improve quality-adjusted life expectancy. The decision tool will be individualized for patient risk factors and available in the electronic health record. This Phase III trial seeks to enroll 60 primary care providers (clusters) and 600 patients aged 40–75 years. Half of providers will be assigned to an intervention to utilize the decision tool with approximately 10 patients each, and half will be assigned to usual care. Mixed-methods follow-up will include collection of preventive care utilization from electronic health records, patient and physician surveys, and qualitative interviews. We hypothesize that quality-adjusted life expectancy will increase by more in patients who receive the intervention, as compared with controls.

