### Intervention

PDP will randomize providers (clusters) to receive access to individualized recommendations via the EHR for eligible patients (“intervention”) or usual care (“control”, chosen as a benchmark for current preventive care delivery). Trial design is a parallel, partially blinded, 1:1 allocation ratio. Intervention arm providers will be asked to access individualized recommendations and discuss them with patients. Consent will be via information sheet.

Additionally, utilizing a waiver of informed consent, providers will receive access to the EHR-based decision tool for all of their eligible patients, regardless of whether the study team follows them. We do so because providers may find it easier to remember that individualized recommendations are available for nearly all patients 40–75 years. Also, by encouraging providers to include this step in their clinical workflow, we will maximize chances for widespread adoption.

To accommodate clinical workflow, the model may be executed through a web app accessible in the EHR. Upon execution, the model’s inputs—a patient’s evidence-based risk factors—are automatically extracted from the EHR and individualized recommendations are output, typically within 3 s. The tool will be accessible in 1–2 clicks and will be updated each time the tool is opened. Providers may print the tool and copy/paste it to an after-visit summary (a post-encounter synopsis given to patients in normal workflow), which also is accessible to patients electronically from the health system’s patient portal.

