### Blinding

Because the nature of PDP requires frequent interaction with providers (e.g., intervention feedback), cluster randomization will be unblinded. However, the Principal and Co-Investigators, except the study biostatistician and safety assessor, will be blinded to stratification of outcomes and safety events by arm. The DSMB may request unblinding of specific participants.

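### Study patients are identified after open provider randomization, and the article states neither an order of approach nor masking of those who select, so the primary comparison is exposed to recruitment bias

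*Protocol article*

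**What the plan says.** All of this is in the Methods of the Protocol article, apart from one figure in the Abstract.

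- **Unit of randomization (Intervention):** "PDP will randomize providers (clusters) to receive access to individualized recommendations via the EHR for eligible patients", or usual care, 1:1.
- **Sequence (Providers, under Intervention):** "Those who consent (via information sheet) will be randomized". No patient list is mentioned at that point.
- **Finding patients (Patients, under Intervention):** automated feeds from the health record are linked to upcoming appointments. With these and "manual chart review as needed, the study team will identify specific patients". Two further steps follow: "We will ask if the patient’s provider is willing to discuss individualized recommendations with this patient" and "The team will seek to enroll the patient and remind providers shortly before the scheduled encounter".
- **Number followed (Abstract, Methods; Power):** "approximately 10 patients each" in the intervention arm, and 10 per provider in both arms for the power calculation. The tool itself is open for all eligible patients of intervention providers, whether or not the team follows them.
- **Blinding and Randomization:** "cluster randomization will be unblinded". The principal and co-investigators, apart from the biostatistician and the safety assessor, "will be blinded to stratification of outcomes and safety events by arm". Concealment of the sequence is described only for staff who enroll providers.
- **Inclusion criteria:** patients must be aged 40–75, have at least one high-impact risk factor at a stated threshold, meet at least three of ten listed items, have had at least two primary care visits in 730 days, and have a qualifying visit with their own provider.

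**The concern.** Randomizing providers balances providers. It balances their patients only if patients enter the study by the same rule in both arms. Here patients enter after allocation is open, and the article states no rule for which eligible patients are followed.

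The endpoint is a change over 6 months. How much a patient changes plausibly depends on features visible in a chart, such as recent high readings, past adherence and visit frequency. If staff leaned toward better prospects in one arm, even slightly, the difference in who was picked would appear as a difference in the primary endpoint.

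The planned analysis would not remove it. Modified intention-to-treat starts from patients already selected, so those passed over never enter. A change-from-baseline endpoint deals with starting level but not with expected trajectory.

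**Working it through.** **Step 1: order of events.** Provider consent, then provider randomization (Providers); patients identified, provider asked, patient enrolled (Patients). Allocation is open throughout (Blinding). The stated concealment protects provider enrollment, and the stated investigator blinding covers results by arm. Neither covers the choice of patients.

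**Step 2: do those who select know the arm?** The article does not say so directly. It is a firm inference: allocation is unblinded, and the team asks providers about discussing recommendations that only intervention providers receive.

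**Step 3: SD implied by the plan's own power.** The Power section gives 30 providers per arm, 10 patients each, ICC 0.01, a 3.0-month difference and 86.2% power. It gives no SD, significance level or number of sides. I assume a two-sided 5% test for a difference, with 2 × 30 − 2 = 58 degrees of freedom.

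- Design effect = 1 + (10 − 1) × 0.01 = 1.09.
- SE = SD × √(2 × 1.09 / 300).
- Solving the noncentral t power for 86.2% gives SD ≈ 11.35 months.
- SE = 11.35 × √(2.18 / 300) ≈ 0.97 months; 3.0 / 0.97 ≈ 3.1.

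The 86.2% cannot be reproduced independently, because the SD was solved from it. The second stated figure offers a partial check: with this SD, 54 providers of 10 patients at ICC 0.02 give 79.3%, against the stated 80.4%. The two stated figures are therefore roughly consistent under these assumptions. A normal approximation gives an SD of 11.54 months, and one-sided 5% versions give about 12.7 to 12.9.

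**Step 4: what a selection difference would do.** Suppose there is no true effect, but selection makes expected change differ between arms by b. The rejection rate is the probability that a noncentral t with 58 df and noncentrality b / SE falls beyond ±2.00. The values of b are assumptions; the documents give none.

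| Assumed b (SD) | b (months) | b / SE | False-positive rate |
|---|---|---|---|
| 0 | 0 | 0 | 5% |
| 0.05 | 0.57 | 0.59 | 8.9% |
| 0.10 | 1.13 | 1.17 | 21.1% |
| 0.15 | 1.70 | 1.76 | 40.9% |

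The normal approximation agrees in scale: a 1.0-month shift gives 17.4%.

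**Step 5: the opposite direction.** If a 0.10 SD shift favored controls, a true 3.0-month effect would appear as 3.0 − 1.13 = 1.87 months, and power would fall from 86.2% to about 47%.

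**The case against.** The strongest reply is that this is silence in a condensed article. The article refers to its full protocol for the exclusion criteria and for resolving conflicting data. Order of approach, quota filling and screening logs could well be there too. That stands: one may say only that the article states no order, not that the trial has none.

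A second reply concerns chart review. Automated feeds are the main route and manual review is only as needed. Review may serve just to confirm criteria, since some inputs, such as alcohol use, are less well documented. That also stands, because the text does not say that review is used to choose among eligible patients.

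Third, the inclusion criteria are specific and numeric, and no count of eligible patients per provider is given. How much choice staff have is therefore unknown, and discretion used alike in both arms would not bias the comparison.

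Fourth, the question about the provider's willingness may be the stronger selection route. That is fair, but removing it would still leave the team's own identification of patients without a stated order.

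A reader might infer more: that staff do favor promising patients in the intervention arm, or that 41% estimates this trial's error rate. The documents support neither. They show no differential selection, and the shifts in the table are assumed.

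What remains does not rest on silence alone. The article positively describes patients being identified by the team after open allocation. Objective criteria limit who may be chosen, not who is chosen among those who qualify.

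**Conclusion.** The point holds as a risk of bias, not as a demonstrated bias. In the process described, study patients are identified after open provider randomization, with no stated order of approach and no stated masking of those who select. If patients are picked differently by arm, neither the modified intention-to-treat population nor the change-from-baseline endpoint repairs the comparison.

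The size is unknown. The range of about 9% to 41% rests on a two-sided 5% test, an SD back-solved from the stated power, and assumed shifts of 0.05 to 0.15 SD. It shows that shifts well below the 3.0-month target (0.6 to 1.7 months) would matter. It does not show that they will occur. That those who select know the arm is an inference. The full protocol may already settle the matter.

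**What to change.** Use the same procedure in both arms:

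1. Have the automated feed list each provider's eligible upcoming appointments in a computer-generated random order, or in strict appointment order.
2. Approach patients in that order until the provider's quota is filled.
3. Limit chart review to confirming the listed inclusion and exclusion criteria.
4. Log every patient listed, skipped (with reason), approached and declined, and report these counts by arm.

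The cost is a sort step in an existing feed, a screening log and a short addition to the protocol. Recruitment may be slightly slower where staff would otherwise have taken easier patients. If the full protocol already fixes such an order, nothing need change beyond stating it.

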### Criteria for inclusion in the EHR

Individualized recommendations will be included in the EHR (for on-demand provider access) for any patient aged 40–75 years with a PCP assigned to the intervention arm, who does not meet above exclusion criteria.

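### Patients are put forward after unblinded provider randomization through a willingness question that, as worded, only intervention providers can answer; the article describes no control counterpart

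*Protocol article*

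**What the plan says.** The order of events is set out in the Methods of the protocol article.

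- **Providers (under Intervention).** On randomization: "Those who consent (via information sheet) will be randomized". On access for the intervention arm: "Those who complete the training will receive access to individualized preventive care recommendations in the EHR".
- **Blinding.** The article states that "cluster randomization will be unblinded".
- **Patients (under Intervention).** Candidates are found "Through automated data feeds from the EHR linked with upcoming appointment schedules, and manual chart review as needed". The team then asks if the patient's "provider is willing to discuss individualized recommendations with this patient". The next sentence reads: "The team will seek to enroll the patient and remind providers shortly before the scheduled encounter".
- **Who holds the recommendations.** The first Intervention section says: "Intervention arm providers will be asked to access individualized recommendations and discuss them with patients". Criteria for inclusion in the EHR limits the tool to patients "with a PCP assigned to the intervention arm".
- **Statistical analysis.** The main set is a modified ITT population of patients who completed the baseline encounter, grouped by their provider's allocation. Full ITT and per-protocol sets are possible sensitivity analyses.

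**The concern.** In a cluster trial, randomizing providers balances the patients only if patients enter by the same route in both arms. Here each patient's arm is known when that patient is considered, and the provider is asked a patient-specific question before enrolment is sought. A control provider has no recommendations to discuss, so the question cannot be put to that arm in the same form.

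The screen could plausibly be prognostic. The article's conceptual framework says that what patients do depends on effort, available time, preferences, attitudes and trust in the provider. A patient's own provider can sense these, and the eligibility criteria do not measure them. If providers decline patients partly on such grounds, the enrolled arms differ in expected 6-month change in QALE before the tool has any effect. Readiness to change and the shared decision-making score, both collected in the survey shortly after the baseline encounter, are exposed in the same way.

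The planned analysis cannot repair this. Modified ITT starts from patients with a completed encounter, and full ITT adds back no-shows and cancellations. A patient declined before enrolment is in neither. The missing-at-random assumption of the mixed model concerns missing outcomes among enrolled patients, not who was enrolled.

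**Working it through.** **1. Does the screen act on one arm only?** Setting the sections side by side: providers are randomized at consent; allocation is open; patients are then identified; the provider is asked about the individual patient; enrolment is sought. The tool goes only to trained intervention-arm providers and only for their patients. So the literal question fits the intervention arm alone. Two links are inference: that a refusal stops enrolment, and that control providers are asked nothing comparable.

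**2. The scale of the outcome.** The article gives no SD, alpha or sidedness, so the 86.2% power cannot be computed forward. Assume a two-sided test of the difference at alpha 0.05 and solve backwards from the Power section (3.0 months, 30 providers per arm, 10 patients each, ICC 0.01).

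- Design effect = 1 + (10 − 1) × 0.01 = 1.09
- Effective n per arm = 300 / 1.09 = 275.2
- 86.2% power needs 3.0 / SE = 1.960 + 1.089 = 3.049, so SE = 0.984 months
- SD = 0.984 / √(2 / 275.2) = 11.54 months

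Check against the article's other power figure (54 providers, ICC 0.02, stated as 80.4%): design effect 1.18, effective n = 270 / 1.18 = 228.8, SE = 11.54 × √(2 / 228.8) = 1.079, power = Φ(3.0 / 1.079 − 1.960) = 79.4%. That is close enough to use the SD as a working value. A one-sided alpha of 0.05 would imply an SD of about 12.9 and give 80.2%.

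**3. Size of a possible bias (all inputs assumed).** If a share p is declined in one arm only, that arm's mean shifts by

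bias = p × (mean change in accepted − mean change in declined).

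With no true effect, the two-sided rejection probability is Φ(|bias|/SE − 1.96) + Φ(−|bias|/SE − 1.96).

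| Declined | Gap | Bias (months) | Bias / SE | False-positive rate |
|---|---|---|---|---|
| 10% | 0.5 SD = 5.77 months | 0.58 | 0.59 | 9.0% |
| 20% | 0.5 SD = 5.77 months | 1.15 (38% of 3.0) | 1.17 | 21.7% |

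With the one-sided SD of 12.87 the same shares give 0.64 and 1.29 months.

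The sign may be reversed. With a true effect of 3.0 months and a bias of −0.58 or −1.15, power becomes Φ(2.42 / 0.984 − 1.96) = 69% or Φ(1.85 / 0.984 − 1.96) = 47%.

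**4. A wider range.** Let willingness correlate r with a patient's QALE change, with a fraction f declined: bias = r × φ(z_f) / (1 − f) × SD, where z_f is the f-quantile of the standard normal. For f from 10% to 30% and r from 0.1 to 0.3 (both assumed), the bias runs from 0.23 to 1.72 months and the false-positive rate from 5.6% to 41.6%.

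**The case against.** The best defence is that the article does not say what it is easily taken to say. A reader might infer that a refusal bars the patient; no sentence says so, and the sentence on seeking enrolment carries no condition. A reader might also infer that control patients face no provider screen at all. The Patients section names no arm and does not describe control recruitment separately, and the article refers to a full protocol, not shown here, that may put a parallel question to control providers. Both points stand. The finding has to be conditional on the first and limited to what the article describes on the second.

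There are real safeguards as well. Candidates come from EHR feeds and chart review and must meet numeric risk thresholds, so providers do not choose from an open pool. The primary outcome is a change from baseline, calculated by a model largely from EHR inputs. These narrow the scope for selection. They do not close it, because eligible patients still differ in how likely they are to change.

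A further tempting inference is that the bias must favour the intervention. The article does not support that. Providers might equally pass over patients who seem to need the discussion least, and the article itself treats readiness to change and gain in QALE as separable. Finally, the decline rates and the 0.5 SD gap have no source, and a gap of 5.77 months is nearly twice the target difference. That stands too: the figures show sensitivity and do not estimate what will happen.

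**Conclusion.** The concern holds in conditional form. What the text establishes is a patient-specific provider question, asked after open allocation and before enrolment, that only one arm can answer as worded. If a refusal excludes the patient and no equivalent is asked in the control arm, the comparison is open to recruitment bias that no listed analysis set can undo.

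On the assumed values, the bias would be about 0.6–1.2 months in either direction, with a false-positive rate of about 9%–22% if there is no true effect. This rests on the back-solved SD, 10–20% declined and a 0.5 SD gap; the wider assumptions give 0.23–1.72 months. The documents do not support the stronger conclusion that the primary comparison is invalid or biased in the tool's favour. The point should be fixed before recruitment, because declined patients cannot be recovered later. Confidence is medium, given the two inferences and the unseen full protocol.

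**What to change.** **Preferred.** Replace the willingness question with one arm-neutral question on whether the patient is suitable for the study. Ask it in identical words of providers in both arms, for eligible patients taken in schedule order from the EHR feed. State whether a negative answer excludes the patient, and record and report declines by arm. Because providers know their allocation, their answers could still differ by arm; the reported declines would make that visible. If the full protocol already has such a question for control providers, the article should say so.

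**Alternative.** Drop the provider veto in both arms and record non-discussion as adherence. This removes the screen altogether, but the dilution is not trivial. If 10% or 20% of intervention patients gained nothing, a 3.0-month effect would become 3.0 × 0.9 = 2.7 or 3.0 × 0.8 = 2.4 months. Power would fall to Φ(2.7 / 0.984 − 1.96) = about 78% or Φ(2.4 / 0.984 − 1.96) = about 68%, which might call for more clusters.

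**Cost.** The preferred change is an amendment to the protocol and recruitment script plus a simple decline log. Under the Oversight section, amendments need approval by the IRB, the NIA and the DSMB.

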### Mixed-methods feedback

Patients will be asked to complete two 15–20-min surveys, within 3 business days after the baseline encounter and 6 months later. Surveys will inform overall impressions, select study endpoints and suggestions for future work (Table 4). At 6 weeks and 3 months post-encounter, a team member will call patients to ask if they need another copy of the individualized recommendations or have questions. Providers will be asked to complete a short survey, within 3 business days after each baseline patient encounter. Also, we will conduct qualitative interviews of patients and providers, approximately quarterly, and request regular (informal) provider feedback (Table 4). Qualitative feedback will inform whether the tool is something that patients and providers *want* to use. ﻿Given time constraints in primary care and countless alert messages in the EHR, the tool is only likely to help patients if providers proactively open it in the EHR and discuss with patients. Finally, throughout the study, we will assess preventive (and chronic disease management) service utilization documented in the EHR, which will inform study endpoints. Surveys and qualitative interviews will utilize gift card incentives to promote retention.

**Table 4 Tab4:** Patient and provider feedback

Patients			Providers	
Baseline survey	6 m survey	Qualitative interviews	Regular, informal feedback	Qualitative interviews
**Overall impressions**				
Use of individualized preventive care recommendations during encounter Helpfulness of individualized preventive care recommendations (intervention only) (Likert scale)	Usefulness of individualized preventive care recommendations	Did your doctor talk with you about preventive care during your appointment? Did your doctor give you any written information? What is your opinion of it? How did this visit compare with other visits you have had with your doctor?	What did you like about the tool? Dislike? How often do you use the tool? Why (why not)?	What value did the decision tool add to patient encounters? What is an example of when the tool enhanced communication about preventive care? When it did not help?
**Use of shared decision-making**				
Use of shared decision-making (SDM-Q-9) [25, 26]	-	How did your doctor involve you in that conversation? What was most helpful? What could be improved?	Would you please tell me a bit about how you discuss the tool with patients?	Did the tool encourage shared decision-making? Please explain.
